## Abstract

**Background:**

The incidence of gastric cancer in East Asia is much higher than the international average. Therefore, improving the prognosis of patients and establishing effective clinical pathways are important topics for the prevention and treatment of gastric cancer. At present, the enhanced recovery after surgery (ERAS) pathway is widely used in the field of gastric surgery. Many randomized controlled trial (RCT) studies have proven that the ERAS regimen can improve the short-term clinical outcomes of patients with gastric cancer. However, a prospective study on the effect of the ERAS pathway on the prognosis of patients with gastric cancer has not yet been reported. This trial aims to confirm whether the ERAS pathway can improve the disease-free survival and overall survival of patients undergoing laparoscopic-assisted radical resection for distal gastric cancer.

**Methods/design:**

This study is a prospective, multicentre RCT. This experiment will consist of two groups – an experimental group and a control group – randomly divided in a 1:1 ratio. The perioperative period of the experimental group will be managed according to the ERAS pathway and that of the control group will be managed according to the traditional management mode. An estimated 400 patients will be enrolled. The main endpoint for comparison is the 3-year overall survival and disease-free survival between the two groups.

**Discussion:**

The results of this RCT should clarify whether the ERAS pathway is superior to traditional treatment on inflammatory indexes, short-term clinical outcome and survival for laparoscopic-assisted radical resection of distal gastric cancer. It is hoped that our data will provide evidence that the ERAS pathway improves survival in patients with gastric cancer.

**Trial registration:**

Chinese Clinical Trial Registry, CHiCTR1900022438. Registered on 11 April 2019.

## Introduction

### Background and rationale

Gastric cancer is a common malignant tumour with the third highest mortality rate worldwide. In 2018, more than 1.3 million new cases of gastric cancer were diagnosed and more than 780,000 deaths occurred [1]. Although the incidence of gastric cancer has decreased in the past 30 years, it is still very high in East Asia [2]. Indeed, there are more than 400,000 new cases of gastric cancer in China each year. The overall 5-year survival rate of these patients is about 30%, which is significantly lower than that in South Korea and Japan [3]. Overall, improving the comprehensive treatment effect of gastric cancer, ensuring the quality and safety of the perioperative period, improving the prognosis of these patients, and establishing an effective clinical pathway are important topics of research in China, and the primary goals are preventing and treating gastric cancer. At present, many treatment methods, such as surgery, radiotherapy, chemotherapy, targeted therapy, and immunotherapy, are available for patients with gastric cancer. Surgical resection is an effective way to improve the survival rate of these patients. Among the surgical options available, D2 radical gastrectomy has become the standard method for advanced gastric cancer. Since Goh et al. first reported laparoscopic radical gastrectomy for advanced gastric cancer in 2001, laparoscopic gastric cancer surgery has been developed rapidly and is used worldwide, especially in countries with a high incidence of gastric cancer, such as Japan, South Korea and China [4]. One of the unique advantages of laparoscopic surgery is its minimally invasive nature, but in view of the need for D2 lymph node dissection for patients with advanced gastric cancer, this operation is difficult and complex, so initial laparoscopic surgery is used only for the treatment of early-stage gastric cancer. After more than 10 years of research, large samples of multicentre clinical data have confirmed the safety, feasibility and effectiveness of laparoscopic radical gastrectomy for the treatment of early gastric cancer [5]. The latest Chinese Laparoscopic Gastrointestinal Surgery Study-01 (CLASS-01) findings state that “laparoscopic distal gastric cancer D2 radical resection performed by an experienced team is safe and feasible for the treatment of locally advanced gastric cancer” [6]. Upon reviewing the development of and advancements in gastric cancer surgery, we find that it has gradually changed from “standard and open surgical resection” to “individualized and accurate minimally invasive surgery” with further improvements to the safety of the operation and the quality of life of the patients postoperatively [7]. The new approach guided by the concept of laparoscopic minimally invasive surgery not only reduces the size of the surgical incision but also minimizes tissue trauma and maximizes functional preservation on the basis of radical oncology [8].

The concept of enhanced recovery after surgery (ERAS) was first proposed by Kehlet and is considered an important milestone in the development of surgery in recent years [9]. Its core goal is to adopt a series of optimized measures performed during the perioperative period on the basis of evidence-based medical findings to reduce the physiological and psychological stress of patients and to accelerate their recovery [10]. In contrast to traditional perioperative management, ERAS combines new techniques in anaesthesiology, pain, nutrition, psychology and surgery with traditional perioperative management by integrating medical interventions to accelerate the postoperative rehabilitation of surgical patients and ultimately improve their clinical outcome [11]. Our centre published the results from the first international randomized controlled trial (RCT) on the effect of ERAS on the short-term outcomes of postoperative patients with gastric cancer, proving that, compared with the traditional perioperative treatment regimen, the ERAS regimen is safe and feasible for perioperative gastric cancer patients. ERAS can reduce postoperative stress, shorten hospital stay, and improve patient quality of life, and it does not increase the incidence of postoperative complications [12]. Recent studies have shown that surgical stress can also affect the long-term oncological results of digestive tract tumours [13]. The mechanism underlying this effect may be immunosuppression as well as changes in the immune response, leading to a higher recurrence rate and more distant metastases. Surgical trauma can cause local and systemic inflammation, which can also result in the rapid growth of residual and micrometastatic diseases [14–16]. The ERAS pathway can reduce the systemic inflammatory response and facilitate early reversal of the human stress response, and it has been shown to significantly reduce the incidence of postoperative complications; thus, it has the potential to improve long-term oncology results. These results suggest that the application of the ERAS management pathway may not only improve short-term outcomes such as hospitalization days, postoperative complications, and mortality but also benefit tumour patients in terms of long-term survival. Ljungqvist et al. showed that ERAS pathway management played a positive role in the long-term survival of patients with colorectal cancer [17]. However, a prospective study investigating the effect of the ERAS pathway on the prognosis of gastric cancer has not yet been reported.

## Objectives

The purpose of this study is to investigate the impact of perioperative ERAS pathway management on the clinical safety and prognosis of patients undergoing laparoscopic-assisted distal gastric cancer radical surgery.

## Trial design

This experiment will include patients randomly divided into two groups – an experimental group and a control group – in a 1:1 ratio. The perioperative period of the experimental group will be managed according to the ERAS pathway and that of the control group will be managed according to the traditional management. After the patient was admitted to the hospital, imaging and haematological examinations will be performed; the risk assessments of nutrition risk screening 2002 (NRS2002), vein thromboembolism, American Society of Anesthesiologists will be administered; contraindications will be excluded; and laparoscopic-assisted radical resection of distal gastric cancer (D2, Billroth I, Billroth II, Roux-en-Y) will be performed under anaesthesia.

The trial will assess the clinical safety of the ERAS pathway and its impact on long-term survival. The effect of the ERAS pathway on inflammatory factors – leukocyte count, neutrophil percentage, C-reactive protein (CRP), procalcitonin, tumour necrosis factor-alpha (TNF-α) and interleukin-6 (IL-6) – will also be explored. The sample size is calculated according to survival rate, follow-up time, inferior value, grouping ratio, test efficiency, and loss of follow-up rate. A complete checklist of items according to SPIRIT (Standardized Protocol Items: Recommendations for Intervention Trials) (2013) is provided [18].

## Methods: Participants, interventions and outcomes

### Participant selection and randomization

Patients who have a diagnosed middle and lower gastric adenocarcinoma and who underwent laparoscopic-assisted radical resection of distal gastric cancer will be recruited from the 13 hospitals listed in Table 1. To achieve adequate enrolment, all surgeons in the gastrointestinal departments of the cooperating hospitals have been informed of this trial. Patients will be recruited for the study from the gastrointestinal surgery or gastrointestinal surgery outpatient clinic or by referral from the local affiliated hospital. The enrolment period is expected to be completed within 10 months from the beginning of recruitment. A total of 400 eligible patients will be selected and randomly (1:1) enrolled in the ERAS group and the traditional treatment group. Figure 1 shows the test group selection flowchart.

**Table 1 Tab1:** The 13 participating surgical centres

Number	Centre	Department and investigator
1	Affiliated Hospital of Qingdao University	Gastrointestinal Surgery, [name]
2	Shandong Provincial Hospital	Gastrointestinal Surgery, [name]
3	Qilu Hospital of Shandong University	Gastrointestinal Surgery, [name]
4	Qianfoshan Hospital of Shandong Province	Gastrointestinal Surgery, [name]
5	Second Hospital of Shandong University	Gastrointestinal Surgery, [name]
6	Yantai Yuhuangding Hospital	Gastrointestinal Surgery, [name]
7	Weihai Municipal Hospital	Gastrointestinal Surgery, [name]
8	Weifang People’s Hospital	Oncological Surgery, [name]
9	Dongying People’s Hospital	General Surgery, [name]
10	Rizhao People’s Hospital	General Surgery, [name]
11	Qingdao Municipal Hospital	Gastrointestinal Surgery, [name]
12	Jining People’s Hospital	Gastrointestinal Surgery, [name]
13	Weihai Central Hospital	Gastrointestinal Surgery, [name]

**Fig. 1 Fig1:**
[figure not shown]
Flowchart of patient enrolment and randomization. *Abbreviations*: *ERAS* enhanced recovery after surgery, *POD* postoperative day.

For randomization, a central dynamic, stratified strategy is adopted. The randomization sequence is generated by using the Pocock–Simon minimization method in SAS version 9.3 (SAS Institute Inc., Cary, NC, USA) and stratified by participating site (13 hospitals) and surgical procedure (laparoscopic or robotic). Participating centres will submit the above information to the data centre at the Department of Gastrointestinal Surgery, Affiliated Hospital of Qingdao University, Qingdao, China, where central randomization will be performed. Information on treatment allocation is subsequently sent to each participating centre.

The inclusion criteria were as follows: (1) newly treated patients with no chemotherapy, radiotherapy or other anti-tumour treatment performed before the beginning of the clinical trial; (2) patients between 18 and 75 years of age; (3) patients at a clinical stage of advanced T (1–4a), N (0–3) or M0 scheduled to undergo radical resection of distal gastric cancer; (4) male or non-pregnant and lactating females; (5) patients with pathologically diagnosed gastric adenocarcinoma; (6) patients with Eastern Cooperative Oncology Group (ECOG) score 0–1; and (7) patients who voluntarily sign the informed consent form.

The exclusion criteria were as follows: (1) other malignant tumours within 5 years, (2) M1 disease found during the operation, (3) severe or uncontrolled medical diseases and infections found at the same time, (4) use of opioid analgesics or hormones within 7 days before the operation, (5) severe or uncontrollable mental illness, (6) any unstable condition or condition that may endanger the safety and compliance of the patient, and (7) participation and treatment with anti-cancer drugs in other clinical trials.

### Perioperative management

Before surgery, chest computed tomography (CT), total abdominal enhanced CT, and pelvic CT will be performed to confirm the size and location of the tumour, and distant organ metastasis will be excluded according to evaluations by two experienced radiologists. Upper abdominal CT angiography will be used to evaluate variation in the gastric blood supply of the patients, reduce the risk of intraoperative bleeding and guide lymph node dissection [19]. Echocardiography and pulmonary function tests will be used to evaluate the tolerance of cardiopulmonary function to laparoscopic surgery.

Laparoscopic-assisted radical resection of distal gastric cancer will be performed under general anaesthesia. During the operation, we will follow the basic principles of tumour treatment, master the appropriate scope of gastrectomy, perform fine lymph node dissection and gastrointestinal reconstruction, and record the amount of intraoperative infusion, blood loss, operation time, and use of any opioids or muscle relaxants.

After the operation, any adverse reactions that occur will be closely observed and actively treated. All drugs used will be recorded and described on the case report form (CRF). Laboratory examinations will be performed before the operation and 2 , 4 and 7 days after the operation. The measurements will include routine blood, liver and kidney function, electrolytes, procalcitonin, CRP, IL-6 and TNF-α. For patients with pathological stage II or above, 6–8 cycles of S-1 capsule combined with oxaliplatin adjuvant chemotherapy will be performed. Finally, oncology experts will choose the scheme and duration of treatment in accordance with the actual situation of the patients.

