### Intervention protocols

Laparoscopic-assisted radical resection of distal gastric cancer will be performed by an experienced surgical team from the 13 centres listed in Table 1. Each of these centres performs at least 100 gastric cancer operations per year. Lymph node resection will be performed under laparoscopy, the main anastomosis will be performed with the assistance of a small incision, and the abdominal incision will be less than 8 cm. According to the research programme, the experimental group will actively carry out pre-rehabilitation before the operation, including lifestyle intervention, exercise advice, diet guidance, and health education (outpatient and hospitalization individualized condition consultation and answer). The specific interventions are shown in Table 2. However, target-oriented liquid management and early enteral nutrition (EN) after surgery require special attention. The goals of goal-directed therapy are to maintain central euvolemia while avoiding excess salt and water and a 24-h postoperative fluid balance on + 1 to 1.5 L. Intraoperative detection indicators are as follows: blood pressure, cardiac output, estimated blood loss, end-tidal carbon dioxide, and heart rate. The maintenance fluid flow rate is 1~4 mL kg^− 1^ h^− 1^ (predicted body weight), and large deviations from “zero balance” should be avoided [20]. The well-defined principles for oral intake in the ERAS groups are as follows: drinking a small amount of water and chewing xylitol on the day of operation; drinking 500~1000 mL water and chewing xylitol on postoperative day 1 (POD1); oral EN (mainly polypeptide) and chewing xylitol on POD2; oral EN (mainly integrin type) and chewing xylitol on POD3; oral EN, a small amount of semifluid and chewing xylitol on POD4; oral EN, semifluid (mainly) and chewing xylitol on POD5, but the patients in the traditional treatment group began sequential EN support treatment in accordance with the dietary pattern of the ERAS group after anal exhaust.

**Table 2 Tab2:** Perioperative pathway management for gastric cancer

Programme components		ERAS group	Traditional treatment group
Preoperative	***Health education, exercise advice, dietary guidance**	Yes	Yes
	***Organ function evaluation**	Yes	Yes
	***Pre-rehabilitation treatment**	Yes	No
	***MDT, clinical decision making**	Yes	Yes
	***Preoperative nutritional assessment and intervention**	Yes	Yes

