### Study endpoints

The main endpoint is the comparison of 3-year overall survival (OS) and disease-free survival (DFS) between the ERAS pathway group and the traditional treatment group. The secondary endpoints are the total incidence of postoperative complications, incidence of major complications, 30-day re-hospitalization rate, 30-day mortality rate, hospitalization days and hospitalization costs as well as other short-term clinical outcomes. The exploratory results are changes in inflammatory indexes (i.e., leukocytes, neutrophil percentage, CRP, procalcitonin, TNF-α and IL-6).

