### Discharge criteria

The criteria for discharge are as follows: (1) postoperative pain score with oral analgesics controlled well (visual analogue scale score below 4), (2) oral semifluid food without intravenous rehydration, (3) satisfactory exercise regimen (6 h a day or up to preoperative level), (4) adequate out-of-hospital care, (5) voluntary discharge of the patient, and (6) no surgical complications, such as fever, abdominal pain, or infection. In addition, the contact information and address of each patient will be confirmed before discharge. Follow-up will be conducted by telephone within 24 h after discharge, and the focus will be on dietary tolerance, pain, defecation and any discomfort.

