### Follow-up

After the operation, a special follow-up team will be responsible for performing patient follow-up, and the first outpatient review will begin at 3 weeks after the end of treatment.

From 0~2 years after the operation, follow-up every 3 months will include a routine blood examination, an analysis of biochemical markers and digestive tract tumour indicators, and imaging examinations. In addition, endoscopic examinations will be performed once a year. At each follow-up, the adjuvant treatment, postoperative recovery, and short-term and long-term side effects will be assessed, as shown in Fig. 2. From 2~3 years after the operation, follow-up will occur every 6 months, as outlined above.

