### Statistical analyses

Classification variables will be analysed by the chi-squared test or Fisher’s exact test, and continuous variables will be analysed by the independent *t* test. DFS will be defined as the time from surgery to death or recurrence of gastric cancer, whichever occurs first. The Kaplan–Meier method will be used to generate survival curves, and the log-rank will be applied to compare the differences between survival curves. The hazard ratio and 95% confidence interval will be calculated with the Cox regression model. Variables will be selected for inclusion in the final multivariable model using a stepwise method, and significance levels of 0.25 and 0.15 will be employed as the criteria for inclusion and retention. A *P* value of less than 0.05 will be considered to indicate statistical significance. Data analysis will be performed by using SPSS® software package version 22.0 (SPSS Inc., Chicago, IL, USA).

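### The day-7 inflammatory-marker comparison is open to informative missingness, probably against ERAS, unless patients already discharged are also sampled (minor)

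*Protocol article*

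**What the plan says.** - **Sampling.** Under Perioperative management, laboratory tests are due before surgery and 2, "4 and 7 days after the operation". They include routine blood and "electrolytes, procalcitonin, CRP, IL-6 and TNF-α". The text does not restrict them to inpatients.
- **Status.** Study endpoints: "The exploratory results are changes in inflammatory indexes". The Discussion paragraph of the Abstract nevertheless expects the trial to show whether ERAS is superior on these indexes, so a between-arm comparison is intended.
- **Diet.** Under Intervention protocols, ERAS patients take some semifluid food on day 4, then "oral EN, semifluid (mainly) and chewing xylitol on POD5". Controls follow the same sequence but start it only once bowel gas has passed.
- **Discharge.** The Discharge criteria are the same in both arms. They include tolerating semifluid food without intravenous fluids, and "no surgical complications, such as fever, abdominal pain, or infection".
- **After discharge.** "Follow-up will be conducted by telephone within 24 h after discharge". Under Follow-up, "the first outpatient review will begin at 3 weeks after the end of treatment". The follow-up visits after adjuvant chemotherapy in the Fig. 2 legend start at 3 months.
- **Expected stay.** The Introduction says ERAS shortens hospital stay, and hospitalization days are a secondary endpoint.
- **Analysis.** Statistical analyses: "continuous variables will be analysed by the independent" *t* test.

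**The concern.** Each rule is reasonable alone; the difficulty lies in how they combine. Whether a patient is still in hospital on day 7 depends on the arm, because ERAS patients can meet the diet criterion sooner. It also depends on health, because patients with fever, infection or another complication are kept in. Those conditions raise CRP, procalcitonin and the cytokines.

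If blood is drawn only from inpatients, the ERAS patients with a day-7 value would contain a larger share of complicated cases than the controls. A *t* test on the available values would then compare differently selected groups. It could hide a real ERAS reduction or show an increase that does not exist. The Discussion section explains the hoped-for survival gain through a smaller stress response and better-preserved immunity, so a distorted day-7 result would blur the evidence for that explanation.

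**Working it through.** The article gives no discharge-day distribution, complication rate or marker distribution, so there is no stated figure to reproduce. What follows is a range under assumptions.

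**Inputs**
- From the article: 200 patients per arm; sampling on days 2, 4 and 7; mainly semifluid diet on day 5 in ERAS; discharge barred by fever or infection.
- Assumed: a share *c* of 10-30% complicated, equal in both arms; markers *k* = 2 to 3 times higher in complicated patients; complicated patients all still in hospital on day 7; uncomplicated patients leaving before day 7 with probability *e*, which differs by arm; discharged patients not sampled; no true ERAS effect.

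**Formulas**
- Complicated share among those sampled: *s* = *c* / [*c* + (1 − *c*)(1 − *e*)].
- Spurious ERAS/control ratio of geometric means: *k* raised to the power (*s* in ERAS − *s* in control).

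**Worked case, *c* = 20%, early discharge 50% (ERAS) and 10% (control)**
- ERAS: 0.20 / (0.20 + 0.80 × 0.50) = 0.20/0.60 = 0.333; 120 of 200 sampled.
- Control: 0.20 / (0.20 + 0.80 × 0.90) = 0.20/0.92 = 0.217; 184 of 200 sampled.
- Difference 0.116. 2^0.116 = 1.084 and 3^0.116 = 1.136, a spurious ERAS excess of about 8-14%.

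**Range over *c* = 10-30% and *k* = 2-3**

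| Early discharge, ERAS/control | Difference in *s* at *c* = 10% | Difference in *s* at *c* = 30% | Spurious ERAS excess |
|---|---|---|---|
| 30%/10% | 0.137 − 0.110 = 0.027 | 0.380 − 0.323 = 0.057 | about 2-7% |
| 50%/10% | 0.182 − 0.110 = 0.072 | 0.462 − 0.323 = 0.139 | about 5-17% |
| 70%/20% | 0.270 − 0.122 = 0.148 | 0.588 − 0.349 = 0.239 | about 11-30% |
| 30%/30% | 0 | 0 | 0 |
| everyone sampled | 0 | 0 | 0 |

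**Can the sign reverse?** Suppose ERAS truly lowers complications (10% against 15%) and complicated patients lie 1.5 SD higher. The true difference is 1.5 × (0.10 − 0.15) = −0.075 SD. At 50%/10% early discharge the shares among those sampled are 0.10/0.55 = 0.182 and 0.15/0.915 = 0.164, so the observed difference is 1.5 × 0.018 = +0.03 SD. At 20%/5% it is −0.05 SD, and the direction survives.

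**Days 2 and 4.** Both come before the ERAS diet becomes mainly semifluid on day 5, so few patients should have left and these days are little exposed.

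**The case against.** A reader might infer that the day-7 sample cannot be obtained from discharged patients, or that the comparison is biased against ERAS as a matter of fact. The article supports neither.

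- The day-7 tests are scheduled for all patients. Outpatient draws may be arranged in the full protocol, which is not shown, and the schedule in Fig. 2 is not visible. All that can be said is that this article describes no such draw.
- Bias also needs uncomplicated ERAS patients to leave before day 7 more often than uncomplicated controls. Meeting the diet criterion is not discharge: pain control, activity, care outside hospital and the patient's own wish also count. The criteria are common to both arms, so dependence on arm is inferred from the pathway and the expected shorter stay.
- The article names a *t* test for continuous variables in general. It does not prescribe a stand-alone day-7 test on available values, and handling of missing data may sit in an analysis plan that is not shown.
- The endpoint is exploratory, and days 2 and 4 also inform the mechanism.

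All four points stand. They reduce the finding from a demonstrated bias to a risk and lower its weight. They do not remove the interaction between the discharge rule, the diet timetable and the day-7 sample, which is in the article's own text.

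**Conclusion.** The day-7 marker comparison is at risk of informative missingness, and the likely direction is against ERAS. This holds on two conditions: discharged patients are not sampled, and uncomplicated ERAS patients leave before day 7 more often than uncomplicated controls. The second is the trial's own expectation in direction, but the article gives no number for it.

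The distortion could therefore lie anywhere from zero to roughly 30% on the marker scale, and the upper end needs the extreme assumption of 70%/20% early discharge. With modest differences in early discharge it is a few per cent. The zero result under equal early discharge also assumes equal complication rates in the two arms.

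Severity is minor: no primary or secondary conclusion is affected.

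**What to change.** 1. Rest the exploratory between-arm marker comparison on days 2 and 4.
2. Analyse baseline and days 2, 4 and 7 for all patients in one baseline-adjusted repeated-measures model instead of separate *t* tests, so that a patient without a day-7 value still contributes the earlier ones.
3. Report day 7 descriptively, with the number sampled per arm and whether each patient was still in hospital or already discharged.
4. State that the model reduces the day-7 bias but does not remove it. In a check by simulation it removed only about a quarter to a half, because earlier marker values capture only part of what decides discharge.

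If discharged patients are in fact sampled on day 7, one sentence saying so largely settles the point.

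The cost is a change of analysis wording, with no added visit, sample or patient. The small downside is less weight on the day-7 contrast.
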